**Fig. 1 Fig1:**
[figure not shown]
Training materials uploaded to a newly developed web-based platform

To ensure satisfactory adherence to the intervention of the self, the project team will telephone contact both the Digital Buddy and the older participants at least once weekly to identify their difficulties participating in the intervention and provide administrative support to help resolve their problems. If some participants within the same cluster miss some training sessions, they will be invited to attend maximally two make-up training sessions after the completion of the 23-h scheduled training programme. In the make-up session, the training contents will be tailor-made for what they have missed. To ensure the availability of access to the Internet, older participants who do not own a smartphone will be provided with a smartphone with a data package complementarily during the study period. There will be no special criteria for discontinuing or modifying allocated interventions.

#### Control group

Participants in the group will receive the usual care. The research team will not provide any form of support to the participants in this group.

### Outcomes

Demographic data will be collected at baseline (T0), including age, gender, education attainment, employment status, financial satisfaction, living arrangement, years of smartphone usage, daily average of internet usage, perceived ability to use a smartphone, and perceived ability to use the internet. Five outcome markers will be measured at both baseline (T0) and the week immediately after the completion of the intervention (T1). The primary outcome is mental well-being. Four secondary outcomes will also be measured, including depressive symptoms, health-related quality of life, self-efficacy, and social support.

#### Mental well-being (primary outcome)

The World Health Organization Five Well-being Index (WHO-5) will be used to measure mental well-being over the past two weeks [33]. WHO-5 comprises five items and each item is rated by a 6-point Likert scale from 0 (at no time) to 5 (all of the time). The total score ranges from 0 to 25. A higher score indicates an increased sense of psychological well-being. The Cantonese version of WHO-5 showed good internal consistency (*α* = 0.86) and good concurrent validity with quality of life (*r* = 0.41–0.51) [33].

#### Depressive symptoms

The 9-item Patient Health Questionnaire (PHQ-9) will be used to measure depressive symptoms over the past two weeks [34]. PHQ-9 comprises nine items and each item is rated by a 4-point Likert scale from 0 (not at all) to 3 (nearly every day). The total score ranges from 0 to 27. A higher score indicates greater severity of depressive symptoms. The Cantonese version of PHQ-9 showed good internal consistency (*α* = 0.82), test-retest reliability (*r* = 0.76), and satisfactory concurrent validity with the mental component of quality of life (*r* = − 0.60) [34].

#### Health-related quality of life

The 12-item Short Form Health Survey Version 2 (SF-12v2) will be used to measure health-related quality of life over the past four weeks [35]. SF-12v2 comprises 12 items rated by scales with varying points measuring eight domains of health, including physical functioning, role physical, bodily pain, general health, vitality, social functioning, role emotional, and mental health. The scores of eight domains are aggregated into two scores: (1) physical component summary score and (2) mental component summary score. The scores will be calculated by a standard algorithm [36]. A higher component summary score indicates a better health-related quality of life. The Chinese version of SF-12v2 showed good test-retest reliability (*r* = 0.67–0.82), and good construct validity with >80% of total variance explained by the two-factor model [37, 38].

#### Self-efficacy

The 10-item General Self-Efficacy Scale (GSES-10) will be used to measure self-efficacy and it was translated and adapted to Chinese. GSES-10 comprises 10 items and each item is rated by a 4-point Likert scale from 1 (not at all true) to 4 (exactly true). The total score ranges from 10 to 40. A higher score indicates better self-efficacy. The Chinese version GSES-10 showed good internal consistency (*α* = 0.91) [39], good criterion validity with wellbeing (*r* = 0.56–0.63, *p* < 0.001), self-esteem (*r* = 0.40–0.49, *p* < 0.001), and mental health (0.39–0.41, *p* < 0.001) [40].

#### Social support

The 12-item Multidimensional Scale of Perceived Social Support (MSPSS-12) will be used to measure perceived social support [41]. MSPSS-12 comprises 12 items which are factored in three subscales by sources of support (i.e. family, friends, significant others). Each subscale comprises four items. Each item is rated on a 7-point Likert scale from 1 (strongly disagree) to 7 (strongly agree). The total score ranges from 12 to 84. A higher score indicates better social support. The Chinese version of MSPSS-12 showed good internal consistency (Cronbach’s *α* = 0.95), good test-retest reliability (ICC = 0.91), and satisfactory concurrent validity with perceived stress (*r* = − 0.221) and caregiving rewarding feelings (*r* = − 0.327) [42].

### Participant timeline

As shown in Table 2, participant recruitment and consenting will take place in the 4 weeks before the baseline. Data collection of demographic and outcome data will take place at the baseline (T0). Interventions including the Digital Buddy and usual care will take place in the intervention period in weeks 1–24. Outcome data will be collected in week 25. Participants allocated to the usual care group will be given a waitlist intervention in weeks 26–49.

**Table 2 Tab2:** Schedule of enrolment, intervention, and assessments (SPIRIT figure)

	Study period			
	Enrolment	Allocation	Post-allocation	Close-out
Week	− 4	0	1–24	25
Timepoint	T0			T1
Enrolment				
Eligibility screen	x			
Informed consent	x			
Allocation	x			
Interventions				
Digital Buddy			x	
Usual care			x	
Assessment				
Demographic	x			
Mental well-being	x			x
Depressive symptoms	x			x
Health-related quality of life	x			x
Self-efficacy	x			x
Social support	x			x

### Sample size

We adopt a prior power analysis using the GPower employing the statistical test of the mean difference between two different groups. We set the level of significance at 0.05, the power at 0.8, and the allocation ratio between the two groups at 1:1. To estimate the effects, we refer to a similar pilot trial examining the effect of an intergenerational mentoring programme [43]. The effect size (i.e. Cohen’s *d*) of the study of the intervention on the primary outcome (i.e. well-being) was 0.5. A sample size of 102 participants is needed. We adopt Hemming’s method to adjust the sample size required under individual randomization for cluster RCT with fixed and equal-sized number clusters [44]. Considering that we will collect data in 6 clusters and assuming that the intra-cluster correlation coefficient (ICC) is 0.01, the estimated total sample size is 244 (i.e. 122 per arm). We assume that the drop-out rate is approximately 20%. A total sample of 292 is estimated, with 146 participants in each arm.

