### Assignment of interventions

As shown in Fig. 2, the cluster randomization method was employed to reduce the risk of within-cluster contamination because most of the training materials are open source that participants share with their peers in a cluster [45]. A permuted block (block size = 6) random allocation sequence list with an allocation ratio to either intervention group or control at 1:1 will be generated by the web-based application www.random.org. The cluster unit of randomization is based on a facility for older adults (e.g. one community centre as a unit). Each unit will be randomly assigned after the entire unit is screened, written consent is obtained, and baseline assessment is completed to reduce the risk of selection bias [46]. A group of six units (i.e. the size of a permuted block) with a similar number of eligible and consented participants will be grouped to be randomly allocated. This aims to ensure each group comprises a similar number of participants. The random allocation process will be implemented by an independent statistician, who will not participate in any other parts of the proposed study. The statistician will assign group labels to each unit based on their sequence of entries with reference to the sequence list, thus ensuring that other members of the research team cannot foresee the group allocations. In this study, only the outcome assessor will be blinded to the group labels. It will not be possible to blind the participants or the interventionists. In the intervention group, we will conduct interventions for the three clusters simultaneously when we have secured the study venues and done the randomization.

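### The cluster-adjusted total of 244 does not follow from its inputs: whole-trial figures went into a per-arm formula and the answer was doubled, and the 80% power claim depends on sidedness and ICC

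*Protocol article*

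**What the plan says.** The Sample size section of the protocol article sizes the trial in three steps.

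1. **Individual randomisation.** The calculation is described as "employing the statistical test of the mean difference between two different groups". The settings are: "We set the level of significance at 0.05, the power at 0.8, and the allocation ratio between the two groups at 1:1". Whether the test is one- or two-sided is not said. The effect size "of the study of the intervention on the primary outcome (i.e. well-being) was 0.5", and 102 participants result.
2. **Clustering.** "We adopt Hemming’s method to adjust the sample size required under individual randomization for cluster RCT with fixed and equal-sized number clusters". With 6 clusters and an ICC of 0.01, "the estimated total sample size is 244 (i.e. 122 per arm").
3. **Drop-out.** An allowance of about 20% brings the total to 292, or 146 per arm.

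The Assignment of interventions section randomises six facilities 1:1 as one block and says of the intervention group that "we will conduct interventions for the three clusters simultaneously". Six is therefore the number of clusters in the whole trial, three in each arm.

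**The concern.** The adjustment for a fixed number of clusters works arm by arm: it takes the individually randomised size of one arm and the number of clusters in one arm. The protocol's 102 and 6 both describe the whole trial, yet the result is labelled per arm and then doubled.

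The formula also treats the between-cluster variance as if it were well estimated. With three clusters per arm it is not.

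The recruitment target of 292 is built on 244. As the paragraph stands, a reader cannot tell whether the trial is larger than its own method requires or short of its stated power. A null result would also be read against an 80% figure that this derivation does not establish.

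**Working it through.** **Inputs.** From Sample size: d = 0.5, alpha 0.05 (sidedness not stated), power 0.8, 102 participants, 6 clusters, ICC 0.01, drop-out 20%. From Assignment of interventions: three clusters in the intervention arm, 1:1 allocation.

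**Step 1: what 102 is.** Two-sample t-test, d = 0.5:
- One-sided 0.05: 51 per arm gives power 0.806 and 50 per arm gives 0.799. The smallest adequate size is 51 per arm, **102 in total**.
- Two-sided 0.05: 64 per arm, 128 in total. With 51 per arm, two-sided power is 0.706.

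So 102 is the total of both arms for a one-sided test.

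**Step 2: reproduce 244.** With n the individually randomised size per arm and k the clusters per arm, the cluster size is

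m = n(1 − ICC) / (k − n·ICC), and the arm size is k·m.

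Entering n = 102 and k = 6:
- m = 102 × 0.99 / (6 − 1.02) = 20.28
- 6 × 20.28 = 121.66, rounded to 122
- taken as one arm and doubled: **244**, as stated.

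None of the other combinations tried gives 244: n = 64 with k = 3 gives 162; n = 102 with k = 3 gives 306; n = 51 with k = 6 gives about 111 to 120; n = 64 with k = 6 gives about 142 to 144; a simple design effect on 102 or 128 gives 118 to 179.

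**Step 3: the same formula with per-arm inputs.**

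| Basis | n per arm | k per arm | m | Per arm | Total |
|---|---|---|---|---|---|
| One-sided, as the 102 implies | 51 | 3 | 51 × 0.99 / 2.49 = 20.28 | 60.83, about 61 | about 122 |
| Two-sided | 64 | 3 | 64 × 0.99 / 2.36 = 26.85 | 80.54, about 81 | about 162 |

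The 122 obtained in Step 2 is thus the total for the trial, not the size of one arm.

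**Step 4: power of the stated size with six clusters.** Comparing cluster means, 3 against 3, leaves 2 × 3 − 2 = 4 df. The critical t is 2.78 two-sided or 2.13 one-sided, against 1.96 or 1.645 for a normal test. With 122 per arm:
- cluster size 122/3 = 40.67
- design effect at ICC 0.01: 1 + 39.67 × 0.01 = 1.397
- non-centrality: 0.5 / √(2 × 1.397 / 122) = 3.30
- non-central t power: 69.9% two-sided, 85.3% one-sided. A simulation of the cluster-mean t-test also gave 69.9% two-sided.

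The protocol assumes ICC 0.01; the other values are my assumptions, to show the range.

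| ICC | Two-sided, 4 df | One-sided, 4 df |
|---|---|---|
| 0.01 | 70% | 85% |
| 0.02 | 60% | 77% |
| 0.03 | 52% | 70% |
| 0.05 | 41% | 59% |

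One-sided power falls below 80% from an ICC of about 0.017.

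**Step 5: the size after drop-out.** 292 less 20% is about 234, or 117 per arm. At ICC 0.01 on 4 df, power is then 69% two-sided or 84% one-sided.

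**The case against.** A reader might infer from Step 4 that this design cannot deliver its stated 80% power. The documents do not support that, for three reasons.

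- **Sidedness.** The protocol nowhere says two-sided, and its 102 is a one-sided figure. On that basis, even with 4 df, power at the protocol's own ICC of 0.01 is 85%, or 84% at 117 per arm.
- **The reference distribution.** The planned analysis is GEE, and a small-sample correction may be specified in an analysis plan that is not shown. With a normal critical value, two-sided power at 122 per arm is 91% at ICC 0.01 and 83% at 0.02. The article's silence on a correction is therefore not itself an error. The normal figure does, however, ignore that only six clusters estimate the variance, so it is a poor basis for a power claim.
- **Direction.** The input slip doubles the formula's answer. It does not shrink the trial.

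All three stand, and they limit the power part of this point to a conditional statement. None touches the arithmetic: whatever the sidedness, ICC or analysis method, the article gives inputs and a result that do not agree.

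**Conclusion.** The cluster-adjusted total is wrong as written. By the protocol's own method and inputs it should be about 122, not 244; on a two-sided basis it should be about 162. This rests on reading 102 as a two-arm total, which the t-test reproduces exactly, and on three clusters per arm, which the protocol states for the intervention group and 1:1 allocation of six implies for the other.

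The 80% power claim is conditional. For the planned size on 4 df it is missed at every ICC from 0.01 upward if the test is two-sided; if one-sided, it is met at ICC 0.01 and missed from about 0.017. These figures assume equal cluster sizes and a comparison of means after the intervention. Any gain from the baseline measurement is left out, because the protocol gives no correlation between the two time points.

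**What to change.** Rewrite the sample size paragraph:

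- State whether the test is one- or two-sided, and give the individually randomised size per arm (51 or 64) accordingly.
- Apply the fixed-cluster formula with that figure and k = 3, and report the result as it comes out (about 122 or 162 in total).
- Keep the planned enrolment, and replace the single 80% figure with the power of that size on 4 df at ICCs from 0.01 to 0.05, both at 122 per arm and at the 117 per arm left after 20% drop-out.

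The cost is one paragraph and a small table, with no extra participants or clusters. The price is a less favourable power statement, clearly so if the test is two-sided.

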**Methods:**

This study will employ a multi-centre, cluster-randomized, two-parallel-group, noninferiority, controlled trial design with a 1:1 group allocation ratio. In the intervention group, a Digital Buddy (i.e. a young volunteer) is assigned to a group of older adults in a 1:10 ratio. A series of training sessions for a minimum of 23 h will be provided to the older adults by Digital Buddy, who will also follow through the intervention period with the older participants. The training contents include ICT and mental health care knowledge and skills. The whole intervention period will last for 6 months between 14 sessions. In the control group, participants will receive the usual care. The primary outcome measure is mental well-being. We aim to recruit 292 older participants. Generalized estimating equations (GEE) will be used to examine the effects of the intervention.

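### The 20% drop-out allowance multiplies by 1.2 instead of dividing by 0.8, so 292 recruits leave about 234, not the stated 244

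*Protocol article*

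**What the plan says.** The Sample size section of the protocol article builds the target in three steps.

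1. For individual randomisation it sets the design values ("We set the level of significance at 0.05, the power at 0.8, and the allocation ratio between the two groups at 1:1"), takes a standardised effect of 0.5 from a pilot trial, and concludes: "A sample size of 102 participants is needed".
2. It adjusts for clustering ("Considering that we will collect data in 6 clusters", with an ICC of 0.01) and reaches 244 in total, 122 per arm.
3. It allows for attrition: "We assume that the drop-out rate is approximately 20%. A total sample of 292 is estimated, with 146 participants in each arm".

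No formula is given for the third step. The Methods paragraph of the Abstract repeats the end result: "We aim to recruit 292 older participants". Nothing elsewhere in the article qualifies either number.

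**The concern.** Three stated numbers, 244, 20% and 292, do not fit together. The purpose of the third step is to enrol enough people that the number from the second step still has outcome data after losses. Drop-out is counted among those enrolled, so the enrolled number must be multiplied by 0.8 to find who is left. Adding 20% to the target is a different operation and always falls short.

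On the plan's own assumption, the trial therefore ends with fewer participants than the plan says it needs. The affected number is the recruitment target, given in both the Abstract and the Sample size section, and later reports are likely to repeat it.

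**Working it through.** **Inputs, all from the Sample size section:** 244 in total (122 per arm) before drop-out; drop-out d = 20%; 292 in total (146 per arm) to recruit; effect 0.5; ICC 0.01; 6 clusters, hence 3 per arm at 1:1 allocation.

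**Reproducing the plan's figure.** Using n × (1 + d):
- total: 244 × 1.2 = 292.8
- per arm: 122 × 1.2 = 146.4, rounded down to 146, and 2 × 146 = 292

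This matches the stated 146 and 292.

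**The allowance that preserves 244.** Using n / (1 − d):
- total: 244 / 0.8 = 305
- per arm: 122 / 0.8 = 152.5, so 153 per arm and 306 with equal arms

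**What 292 delivers.**
- retained at 20% loss: 292 × 0.8 = 233.6, or 116.8 per arm
- shortfall: 244 − 233.6 = 10.4, about 4% of 244
- loss that 292 can absorb: 1 − 244/292 = 16.4%
- under-enrolment: 305 − 292 = 13, or 14 with equal arms

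**Effect on power.** With n per arm and m = n/3 per cluster, the design effect is 1 + (m − 1) × 0.01, the effective size per arm is n divided by the design effect, and the non-centrality is 0.5 × √(effective size / 2).

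- At 122 per arm: m = 40.67, design effect 1.397, effective size 87.4.
- At 116.8 per arm: m = 38.93, design effect 1.379, effective size 84.7.

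The protocol does not state the sidedness of the test or a degrees-of-freedom correction, so four conventions are shown. The 4 cluster-level degrees of freedom are 6 clusters minus 2.

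| Reference distribution (alpha 0.05) | 122 per arm | 116.8 per arm |
|---|---|---|
| Individual-level df, one-sided | 95.1% | 94.5% |
| Individual-level df, two-sided | 90.8% | 90.0% |
| 4 df, one-sided | 85.3% | 84.4% |
| 4 df, two-sided | 69.9% | 68.6% |

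The slip costs between 0.6 and 1.3 percentage points. The level below 70% in the last row comes from having only six clusters and is already present at 244.

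**Status of the 244.** A two-sample t-test with the stated inputs gives 102 in total one-sided (51 per arm) and 128 two-sided (64 per arm), so 102 is the one-sided figure. The formula for a fixed number of clusters is m = n(1 − ICC)/(k − n × ICC), with n the individually randomised size per arm and k = 3:
- one-sided: 51 × 0.99 / (3 − 0.51) = 20.28 per cluster, 60.8 per arm, about 122 in total
- two-sided: 64 × 0.99 / (3 − 0.64) = 26.85 per cluster, 80.5 per arm, 162 in total after rounding up to 81 per arm

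The stated 122 per arm thus looks like a total that was read as a per-arm number and doubled. Correctly inflated, these totals are 122/0.8 = 152.5 (153) and 162/0.8 = 202.5 (203), both below 292.

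**The case against.** Four points can be made for the plan.

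*The rate is only approximate.* This does not explain 292, because the figure equals 122 × 1.2 per arm to within rounding. A planned loss of 16.4% would hardly be described as about 20%.

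*Multiple imputation keeps everyone in the analysis.* The Statistical methods section plans intention-to-treat with imputation, and the baseline assessment precedes randomisation, so every randomised participant should have baseline data. It is therefore fair to say that about 234 is the number with an observed follow-up outcome, not the number entering the model. The main point survives. There is only one post-baseline assessment, and imputation does not recreate the information lost when it is missing. By inflating for drop-out, the plan itself treats 244 as the number needed with outcomes.

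*244 is not a sound requirement.* This stands. On the stated inputs, 234 exceeds both the one-sided need (122) and the two-sided need (162). The shortfall is against the plan's own number, not against a demonstrated need. But the drop-out step is still wrong, and the same multiplication would under-inflate any corrected base.

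*The effect is trivial.* It is small, as the power table shows. That limits the weight of the point but does not make the stated figures consistent.

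**Conclusion.** The concern holds. Taking 244 and 20% as stated, 292 misses the plan's own requirement by about 10 participants with observed follow-up, and enrolment is 13 too low (14 for equal arms). This rests only on reading drop-out as a proportion of those enrolled. The loss of power is at most 1.3 percentage points with d = 0.5, ICC 0.01 and three equal clusters per arm, and this error alone does not move power from above to below 80% under any of the four conventions checked. It should be corrected because the published target contradicts its own assumption, not because the trial is materially weakened by it. The derivation of 244 and the unstated sidedness are separate and larger questions.

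**What to change.** Correct the statement; do not enrol more on this account. Settle the base figure first, stating the sidedness of the test and the degrees of freedom, and then choose one of these:

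- If 244 is kept, say that 292 enrolled gives about 234 with observed follow-up at 20% drop-out, and quote power at 234 with its assumptions.
- If 244 is kept, say instead that 292 allows for about 16% drop-out.
- If the base is recomputed, divide it by 0.8 and show that 292 covers the result. For the two-sided base of 162 this is 162/0.8 = 202.5, so 203 (204 with equal arms).

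The cost is one restated figure in the Sample size section. The 292 in the Abstract can stay under any of these options.
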